### Participant recruitment and eligibility criteria

PlwD and their informal caregiver will be recruited in the primary care setting through specifically qualified study nurses who work with general practitioners (GP), neurologists, psychiatrists and memory clinics who are in ongoing collaborations and studies with the German Center for Neurodegenerative Diseases (DZNE) at the site Rostock/Greifswald in Mecklenburg-Western Pomerania, a predominantly rural state in the north-eastern part of Germany. Study nurses will act as gatekeepers in this study as they may be perceived as trustworthy by participants due to their previous contact in other studies. Based on the means of recruitment, participants could have been included in other recently completed studies (ClinicalTrials.gov identifiers: NCT04741932, https://clinicaltrials.gov/ct2/show/NCT01401582, NCT03359408, NCT04037501; German Clinical Trials Register Reference No: DRKS00025074, DRKS00013555). After completing these studies, the study nurse checks the patient's and caregiver's eligibility criteria for this study, informs the dyad about the new study if they are eligible, and asks them to participate. If they were willing to participate again, they would be asked to provide written informed consent (IC) and be introduced to the study procedures. If this recruitment path does not yield sufficient participants, we plan to recruit from external settings, such as memory clinics. In some cases, informed consent might require a legal representative when informed consent cannot be acquired from the person with dementia due to severe cognitive impairment.

PlwD should meet the following inclusion criteria: positively screened for dementia through the DemTect procedure (DemTect ≤ 8) (12) or formally diagnosed with dementia by a treating GP, neurologist or psychiatrist. Eligibility criteria for caregivers are as follows: living in the same household or being in contact at least once a day (seeing the patient in person) with the PlwD.

Ethical approval has been obtained from the Local Ethical Committee at the University Medicine Greifswald (Registry number BB128/21 and BB 128/21a). The overall study design is illustrated in Figure 1.

**Figure 1 F1:**
[figure not shown]
Study procedures.

### Sample size

The sample size in qualitative research is driven by data saturation. However, there are no standard criteria for calculating the sample size for this type of study. Blome et al. (9) set their sample size in the process guided by information power. We assume the sample size should be large enough to reveal at least *n* = 20 patients with health state fluctuations. Sun et al. (2) examined a sample size of *n* = 55 patients and found significant associations regarding fluctuations in HRQoL. However, the percentage of patients with dementia reporting health state fluctuations within 14 days is currently unknown. We, therefore, hypothesize that a sample size of *n* = 50 patient and caregiver dyads would be large enough to bear HRQoL outcomes (see health fluctuation outcomes below) and achieve the aims of this study.

### Data collection

At baseline, day seven and day 14, the EQ-5D-5L (13, 14) will be administered *via* standardized face-to-face interviews by dementia-specific qualified nurses at patients' or caregivers' homes. Both patients (self-rating) and caregivers (proxy-rating) will be asked to complete the EQ-5D-5L (in separate rooms). Also, patients' socio-demographic (age, sex, living situation) and the following clinical data will be assessed at baseline: cognitive impairment according to the Mini-Mental State Examination (MMSE) (15, 16), depression according to the Geriatric Depression Scale (17), perceived social support according to the F-SozU (18), deficits in daily living activities according to the Bayer Activities of Daily Living Scale (19), and comorbidity according to the Charlson Comorbidity Index (20, 21). A brief description of the assessed clinical outcome measures is demonstrated in the section “measures.”

After completing the baseline assessment, caregivers will daily self-complete a fluctuation diary for 14 days, documenting the frequency and intensity of health state fluctuations, affected dimensions, and underlying health events (see Figure 2). After completing the fluctuation diary, the diary data will be collected, and the study nurse will conduct a semi-structured interview on day 14 about the documented recurrent health state fluctuations, the possible consideration of these fluctuations in the assessment of health today using the EQ-5D-5L, and appropriate recall periods to capture recurrent fluctuations of HRQoL more accurately in dementia. The questions of the semi-structured interview are displayed in Table 1. Furthermore, guidelines will be drafted, and the nurses will be trained to ensure the replicability of interviews and promote data quality.

**Figure 2 F2:**
[figure not shown]
Health fluctuation diary (exemplary illustration for day 1).

On day seven of the self-completion of the 14-day diary, the nurse will visit the caregiver at their home and will glance over the caregiver's documentation from day 1 to day 7. The study nurse will provide further assistance, discuss inconsistencies in the documented answers and be available for any questions about completing the diary. This could avoid entry errors and missings and, therefore, promotes the retention of protocols. Furthermore, instructions will be provided on how to fill out the diary.

As an incentive for complete follow-up, the patient and caregiver receive a lump sum payment upon completion of the 14-day assessment period.

Before the study roll-out, a pilot study will be implemented for *n* = 5 patients, testing the acceptability, reliability and validity of the used measures. Data collection will take place between October 2021 and December 2022.

### Measures

#### Health-related quality of life and clinical measures

The EQ-5D-5L (13) is one of the most used and well-validated generic patient-reported outcome measures that assess patients' HRQoL today. The EQ-5D-5L comprises both the EQ visual analog scale (VAS), ranging from 0 (worst imaginable health) to 100 (best imaginable health) and a descriptive system comprising five dimensions, namely, mobility, self-care, usual activities, pain/discomfort and anxiety/depression (13). Each dimension has five levels varying from no problems to extreme problems. Each level corresponds to a 1-digit number that expresses the level selected for that dimension ranging from 1 (no problem) to 5 (severe problem), with higher numbers indicating more severe problems (13). These values will be converted to a health utility index using a country-specific value set (14).

The MMSE is the most common tool for assessing the severity of cognitive impairment, categorizing participants into one of four groups of cognitive impairment: without (MMSE value ≥ 27), mild (MMSE values: 20–26), moderate (MMSE values: 10–19), and severe (MMSE values: 0–9) (15, 16). The GDS is a useful screening tool in the clinical setting to facilitate the assessment of depression in older adults, consisting of 15 items. Scores under six are considered normal, depending on age, education, and complaints, and scores above five indicate a hint of depression (17). The F-SozU is a measure of perceived and anticipated social support using 14 items that are rated on a 5-point Likert scale (1 = “does not apply at all” to 5 = “totally applies”) (18). The B-ADL assesses patients' deficits in the performance of everyday activities, comprising 25 items (19). The Charlson Comorbidity Index is the most commonly used comorbidity score to measure the burden of diseases and categorize patients comorbidities based on the International Classification of Diseases (ICD) diagnosis. A weighted sum score could be derived through the absence and presence of different comorbid conditions, with higher scores indicating higher comorbidity (20, 21).

#### Outcome measures to assess health fluctuations

The primary outcomes of this study are (i) the occurrence, frequency and intensity of health state fluctuations documented in the 14-day diary and by using the change in health states from day 1 to day 7 and day 7 to day 14 using the EQ-5D-5L index, the EQ-5D dimensions and the EQ-VAS, (ii) affected HRQoL dimensions, (iii) the underlying health events over time that could have affected patients' health, and (iv) the incorporation of recurrent health state fluctuations in the assessment of health today using the EQ-5D-5L.

i. To assess the frequency and intensity of the health state fluctuation, caregivers document if patients' today's health is much (+2) or somewhat better today (+1), about the same (±0) today, or somewhat (−1) or much (−2) worse today compared to the day before. Also, a repeated administration of the EQ-5D-5L will also assess the health state fluctuation as a self- and proxy-rating at baseline (before starting the diary), seven days after starting the diary, and on the last day of the diary (day 14). The change in the EQ-5D-5L utilities, EQ-5D-5L level scores and level sum scores (LLS), and EQ-VAS scores from day 1 to day 7 and day 7 to day 14 can be used to assess the variability and reliability of each measure.ii. To assign health state fluctuations to specific health dimensions, we will use the health dimension of the diary and the assessment of EQ-5D-5L dimensions at baseline, seven, and 14 days. The caregiver will be instructed to document in the diary which dimensions could be assigned to the fluctuation of today's health state compared to the day before. We will use dimensions of the EQ-5D-5L and two other patient-reported outcomes measures (PROMs), the EQ Health and Wellbeing instrument (EQ-HWB) (22) and the dementia-specific Quality of Life–Alzheimer's Disease (QoL-AD) (23). The EQ-HWB has been designed as a standardized measure of aspects of health and well-being and has 25 items (24). In comparison, the QoL-AD is a widely used measure of the quality of life in dementia diseases that contains 13 items evaluating the domains of interpersonal relationships, financial difficulties, physical condition, memory, mood and overall health. Furthermore, caregivers could specify any other affected dimensions not listed in the diary. All dimensions are shown in Figure 2.iii. Caregivers will also be asked to document any health events that could have caused the health state fluctuations.iv. To evaluate the consideration of past health state fluctuations in the assessment of today's health, the EQ-5D-5L will be administered on day 14. Subsequently, the caregivers will be interviewed and asked whether or not recurrent health state fluctuations (if applicable) were considered in the assessment of health today using the EQ-5D-5L administered minutes before starting the interview. Furthermore, the caregiver will be asked to state what recall period would be more appropriate to assess HRQoL in people living with dementia more accurately.

### Data management

Data management will be conducted according to the guidelines and recommendations for ensuring Good Epidemiological Practice (GEP) (24). Study nurses will collect the socio-demographic and clinical data and the EQ-5D-5L using paper-pencil questionnaires during face-to-face visits with the patients and the caregivers. The diary is also on a paper-pencil basis but will be self-completed by the caregivers and collected by the nurse after completion. A medical documentary transfers all data in electronic Case Report Forms (eCRFs), including automatic plausibility and completeness checks. Physical documents will be stored in a protected place and destroyed after data transfer at the end of the data collection period. The client-server stores all data in the project data management system (25).

### Statistical analyses

#### Quantitative data preparation and analyses

Patient and caregiver characteristics will be demonstrated descriptively. Descriptive statistics will also describe health state fluctuations' occurrence, frequency, and intensity. The occurrence will be operationalized dichotomously: no fluctuations reported vs. at least one fluctuation reported. The frequency will be quantified as the number of fluctuations within 14 days. The intensity will be operationalized as follows: much worse or better = ±2; somewhat worse or better = ±1; about the same = ±0) of the reported health events. We will demonstrate the intensity of the health state fluctuations as a mean change per day with standard deviation.

Furthermore, we will use exploratory data analysis of the EQ-5D-5L data by reporting the number and percentage of patients reporting each level on each dimension of the EQ-5D-5L using simple descriptive statistics (26). The EQ-5D-5L profile and EQ-VAS scores will also be demonstrated using descriptive statistics. Also, change in EQ-5D-5L index, EQ-VAS and LLS will be demonstrated descriptively [mean value of change, Intra Class Correlation (ICC)] over the fluctuation intensity. Furthermore, cluster analyses will be used to identify frequent health events or a combination of events.

To assess the association between occurrence, frequency and intensity of the reported health fluctuation and (i) the differences between the baseline, 7-day and 14-days follow-up EQ-5D-5L profile, health utility and EQ-VAS as well as the (ii) reporting of consideration of these health state fluctuations in the assessment of health today in the EQ-5D-5L, we will use appropriate statistics such as cross tables with ANOVA, *t*-tests and multiple logistic regression models. According to the latter one, multivariate regression models will include the adherence to the recall period (dichotomous: yes, no) as a dependent variable and the fluctuation intensity (low, moderate, high) and further socio-demographic and clinical variables of the patient as an independent variable. We hypothesize that frequent and more intensive health fluctuations reported in the diaries will cause higher variability of the EQ-5D-5L index between baseline and seven or 14 days later and will have higher odds for consideration of these fluctuations in the assessment of HRQoL today (non-adherence to the recall period of today). Additionally, we will use descriptive statistics to identify specific health events most likely affecting the incorporation into the health assessment today. Statistical analysis will be carried out in SAS (version 9.4 M7).

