## Discussion

To the best of our knowledge, this will be the first study evaluating the health state fluctuations in dementia diseases using a daily diary to document the change in today's health compared to the day before over 14 days. This study may reveal important insights into the frequency and intensity of health state fluctuations in dementia, the affected dimensions and underlying health events. Analogous to the findings of Sun et al. (2), we assume that most patients will be affected by health state fluctuations and that these fluctuations impact different health dimensions. Furthermore, we expect to see that health state fluctuations are associated with a higher variation in the assessed HRQoL using the EQ-5D-5L. Therefore, the results of this study may reveal whether and how the five EQ-5D-5L dimensions capture fluctuations in health status in PlwD and whether individuals adhere to the recall period by assessing the extent to which they considered past events and health state fluctuation within their ratings for the health today. If the latter is the case, the interviews will provide information about a more appropriate recall period that captures relevant health state fluctuations and enables a more comparative and in-depth assessment of health status. Like Blome et al. (9), it might be more appropriate to test for EQ-5D-5L several times within a recall period to retain more reliable results.

The information generated from this mixed-methods study can also be vital to inform future research to test modified recall periods of the EQ-5D-5L in PlwD or other fluctuating cyclical health state conditions. The results of this study could make a highly relevant first contribution to more accurate measurements and, thus, give a better understanding of the HRQoL of PlwD. A better understanding of the influences of health state fluctuations on the EQ-5D-5L will make generic PROMs in cyclical health conditions more reliable and generalizable. It will propose a hypothesis on better recall and testing periods for the EQ-5D-5L and other PROMS. Furthermore, the additional information on the presence of fluctuations, the influence of the one-day capture of the EQ-5D-5L and potential changes in this measure necessary to better integrate such information may help to increase the treatment and counseling of patients and their caregivers.

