### Limitations

Due to the COVID-19 situation in Germany, it has to be noticed that recruitment took place under challenging and changing conditions. Especially aged adults are affected by the COVID-19 diseases and the imposed measures to protect against the spread of the disease (28). These circumstances affect the data assessments at patients' and caregivers' homes and might influence recruitment. To accurately monitor health fluctuations and discover the influences of affected health dimensions, this study relies on completing the 14-day diary. Despite checkups on the diary on day 7 and day 14, caregivers might still miss reporting health state fluctuations on days that they are unsupervised and thus might underestimate the influence of health state fluctuations.

Additionally, there are significant differences in the perception of health status between the caregiver and the patient (self and proxy). Findings reported by the caregiver might pronounce the caregiver's perspective on health state fluctuations in PlwD (29, 30). We will address these problems by triangulating our quantitative findings with the interview findings and focusing on the patient's perspective in multivariable regression models.

Finally, the scope of this study will be limited to the federal state of Mecklenburg-Vorpommern. However, previous studies in dementia care research in this state have shown that findings are generalizable to other results nationwide.

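### If most patients fluctuate, the none-versus-any split may leave a small reference group, and the raw 14-day count falls with each uncompleted diary day

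*Protocol article*

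**What the plan says.** All references are to the protocol article. Under Outcome measures to assess health fluctuations, the caregiver rates each day on a five-point scale from +2 to −2; the categories below the top one read "or somewhat better today (+1), about the same (±0) today, or somewhat (−1) or much (−2) worse today compared to the day before". No minimum size is given for a change to count.

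Quantitative data preparation and analyses then fixes two summaries:

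- Occurrence, as a dichotomy: "no fluctuations reported vs. at least one fluctuation reported".
- Frequency: "The frequency will be quantified as the number of fluctuations within 14 days".

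The same section relates occurrence, frequency and intensity to differences in the EQ-5D-5L and EQ-VAS between visits, and to reported consideration of fluctuations in the rating of health today. It names cross tables with ANOVA, t-tests and logistic regression as examples of methods. The stated hypothesis concerns frequency and intensity, and the one regression model that is spelled out uses intensity in three levels.

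Under Sample size, the 14-day share of patients with fluctuations is called unknown, and the target is put as "We assume the sample size should be large enough to reveal at least" 20 patients with fluctuations. No minimum is set for patients without them. The Discussion says "we assume that most patients will be affected by health state fluctuations". Limitations concedes that "caregivers might still miss reporting health state fluctuations on days that they are unsupervised".

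**The concern.** Two features of the stated definitions can weaken the association analyses.

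**Threshold.** Read literally, a single rating of somewhat better on one day in 14 places a patient in the fluctuation group. That is the lowest possible threshold. If most patients cross it, the comparison is limited by the patients who do not, and the sample-size argument says nothing about their number.

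**Count.** Frequency has no denominator. A day with no entry cannot add to the count, so a patient with an incomplete diary looks more stable than one with the same course and a full diary. The hypothesis rests partly on this variable. If completeness is related to the patient's condition or the caregiver's load, the association itself could be distorted, and not only the average count.

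The coding also shapes what is counted. Each rating refers to the day before, so a one-day dip that recovers (−1, then +1) gives two entries, while a lasting step (−1, then zeros) gives one. Frequency is therefore a count of day-to-day changes, not of episodes.

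**Working it through.** **Inputs from the document.** n = 50 dyads; 14 daily ratings; at least 20 patients with fluctuations wanted; most patients expected to be affected. **Assumed here, because the article gives no values:** two-sided 5% level, 80% power, the occurrence shares, and the daily rates used below.

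**1. The sample-size figure.** The 50 cannot be reproduced, because no effect size, power or prevalence is stated. The only check is the implied share, 20/50 = 40%. The exact binomial probability of at least 20 fluctuating patients among 50 is 0.55 if the true share is 40%, 0.94 at 50%, and above 0.99 at 60%. If most patients fluctuate, the target is met almost automatically and hardly constrains n.

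**2. Size of the reference group.** Expected number without fluctuations = 50 × (1 − share). The detectable standardised difference is the solution of the two-sample t-test power equation for the two group sizes. It is close to (1.96 + 0.84) × √(1/k + 1/(50 − k)), where k is the number without fluctuations.

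| Share with at least one | k without vs. with | Normal approximation (SD) | t-test (SD) |
|---|---|---|---|
| 50% | 25 vs. 25 | 0.79 | 0.81 |
| 60% | 20 vs. 30 | 0.81 | 0.83 |
| 80% | 10 vs. 40 | 0.99 | 1.01 |
| 90% | 5 vs. 45 | 1.32 | 1.35 |

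Worked case at 80%: 2.80 × √(1/10 + 1/40) = 2.80 × 0.354 = 0.99. The power to detect 0.8 SD (t-test) falls from 0.79 at 25 vs. 25 to 0.60 at 10 vs. 40 and 0.38 at 5 vs. 45.

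**3. How likely such shares are.** With independent days and the same daily rate p in every patient, the share is 1 − (1 − p)^14. For p = 5, 10, 15 and 20% this gives 51, 77, 90 and 96%, leaving about 24, 11, 5 and 2 of 50 without fluctuations. If patients differ in their rates (beta-binomial, within-patient correlation 0.1 to 0.5), about 20 to 36 of 50 remain without fluctuations at a mean daily rate of 10%, about 8 to 25 at 20%, and about 3 to 17 at 30%. The split may be badly unbalanced or nearly even; the document does not settle which.

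**4. Count with incomplete diaries.** If blank days fall at random, expected count = true change days × completed days / 14. For an illustrative patient with six true change days and 10 completed days, 6 × 10/14 = 4.3. This holds whatever the share in step 2.

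**The case against.** The strongest reply is that the study is explorative, that its hypothesis and its only specified regression rest on frequency and intensity, and that the text does not tie any particular test to occurrence. This stands, and it limits the damage: what is at risk in the none-versus-any contrast is one secondary analysis.

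A reader might go further and infer that occurrence will be almost universal, so that the variable is close to constant. The document does not support that. It calls the share unknown and assumes only a majority, and step 3 shows that shares of 90% and above depend on the assumed daily rate and on how alike patients are. A reader might also infer that the target of 20 protects the wrong group. That is not supported either. Patients with fluctuations are the right group for describing affected dimensions and events and for asking about recall. The target is incomplete only for the occurrence comparison.

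On the count, it can be said that rules for missing days belong in an analysis plan, and that the article provides a day-seven nurse check, diary instructions, a payment on completion and completeness checks at data entry. These reduce blank days but do not remove them. The article itself fixes frequency as a plain number within 14 days while conceding unreported days, and it does not say how blank days are scored.

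Redefining a fluctuation as a departure followed by a reversal would be debatable. The stated construct is change since the day before, and a change on the last diary day could not be classified. That is no reason to replace the definition.

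**Conclusion.** The point holds in a limited form. Occurrence uses the lowest possible threshold and is listed as an association variable, while n = 50 is argued only from patients with fluctuations. If the authors' own expectation of a majority is right, the reference group may be small: at 80 to 90% occurrence, about 10 to 5 of 50, with detectable differences of about 1.0 to 1.35 SD. Such a contrast could be estimated, but very imprecisely. At shares near 50 to 60% this concern largely disappears. These figures rest on the assumed shares, level and power.

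The frequency point does not depend on the share. A raw count without a denominator undercounts patients with incomplete diaries, by a factor of completed days over 14 if blanks fall at random, and it enters the main hypothesis. The actual extent of blank days is not known from the document.

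**What to change.** - Report occurrence as a descriptive figure only, and base the associations on frequency and intensity, which are already planned.
- Express frequency as non-zero days per completed diary day. Where it is modelled as a count, use the log of completed days as offset. Treat blank days as missing, not as zero.
- Describe frequency as a count of day-to-day changes. As a descriptive supplement, report how many were followed by a move in the opposite direction, so that lasting steps and reversals can be told apart.

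The cost is revised analysis wording, slightly more analysis work and the loss of the none-versus-any test. No further data or patients are needed. An offset corrects only for the number of days observed; it does not help if blank days differ systematically from completed ones, so diary completeness should be shown beside the result.

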#### Qualitative data preparation and analysis

The qualitative interviews will be transcribed, coded using NVivo (version 12, Germany) and analyzed thematically (27). A thematic analysis consists of the following stages: (i) familiarization, (ii) identifying a thematic framework, (iii) indexing, (iv) charting, and (v) mapping and interpretation. This approach is generally considered more appropriate when the data collection tends to be more structured and there are pre-determined issues to explore. As such, a deductive approach will be used with a pre-determined framework around the following themes: occurrence and frequency of health fluctuations, the intensity of fluctuation, affected dimensions, and recall period. To increase validity of qualitative research results, two independent researchers will analyze the interviews separately, and checkups, will be made in the beginning to test for consistency and widely disparate coding.

Results of the thematic analysis of the semi-structured interviews will be compared with the results of the diaries and the EQ-5D-5L assessment to demonstrate how often and intensively health fluctuates in our sample of 50 patients with dementia, what dimensions were affected by these fluctuations, whether documented past events and health fluctuations were considered in the assessment of health today using the EQ-5D-5L, and what recall period would be more appropriate from the perspective of the caregivers to assess health status in such fluctuating conditions.

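### Intensity, summarised as a mean change per day, does not isolate the size of fluctuations: in absolute values it mostly repeats frequency, and in signed values it cancels

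*Protocol article*

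**What the plan says.** Occurrence, frequency and intensity are listed among the primary outcomes (Outcome measures to assess health fluctuations). The caregiver's daily rating is directional, from much better (+2) down to worse: "or somewhat (−1) or much (−2) worse today compared to the day before".

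The section Quantitative data preparation and analyses then fixes the two measures:

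- Frequency: "The frequency will be quantified as the number of fluctuations within 14 days".
- Intensity, coding: "much worse or better = ±2; somewhat worse or better = ±1; about the same = ±0) of the reported health events".
- Intensity, summary: "We will demonstrate the intensity of the health state fluctuations as a mean change per day with standard deviation".

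It names both attributes in the hypothesis: "We hypothesize that frequent and more intensive health fluctuations reported in the diaries will cause higher variability of the EQ-5D-5L index". The same sentence extends this to higher odds that past fluctuations are considered when health today is rated.

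The regression takes "adherence to the recall period (dichotomous: yes, no) as a dependent variable". Its predictors are "the fluctuation intensity (low, moderate, high) and further socio-demographic and clinical variables of the patient as an independent variable". The number of fluctuations is not in that list.

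**The concern.** An intensity measure should say how large the fluctuations are when they occur. A per-day average on a scale with a zero for unchanged days also depends on how many days fluctuate. Size on a fluctuation day can only be 1 or 2, whereas the number of such days runs from 0 to 14, so the count can be expected to drive the average. If positive and negative ratings are averaged with their signs, a patient who swings up and down can score zero.

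The hypothesis gives frequency and intensity separate roles. If the intensity term in the adherence model were built from this average, with no frequency term beside it, an association due to the number of fluctuation days could be read as an effect of their severity. A real effect of severity could be missed.

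**Working it through.** There is no figure in the article to reproduce for this measure. The sample of 50 dyads is set by judgement, without alpha, power or effect size.

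**1. Identity (absolute values, all 14 days).** Let k be the number of fluctuation days and m the number of those rated ±2. The absolute changes sum to k + m, so

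mean absolute change per day = (k + m)/14 = (k/14) × (1 + m/k).

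The first factor is frequency. The second is mean size on fluctuation days, confined to 1 to 2.

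**2. Ranking example.**

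- Patient A, ten days of ±1: (10 + 0)/14 = 0.71; size on fluctuation days 1.
- Patient B, four days of ±2: (4 + 4)/14 = 0.57; size on fluctuation days 2.

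A, with only small changes, ranks as more intense than B, with only large ones.

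**3. Signed values.** Ten fluctuation days, five of +1 and five of −1, give (5 − 5)/14 = 0, the same as a patient who never changed.

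**4. How much of the summary is frequency.** The article gives no fluctuation rates, so these are assumptions: fluctuation on about 5 of 14 days; the daily probability varying between patients as beta(1.5, 2.5), beta(3, 5) or beta(6, 10); the probability that a fluctuation is rated ±2 varying as beta(2, 4), independent of frequency.

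| Summary | Correlation with frequency | Correlation with tendency to large changes |
|---|---|---|
| Mean absolute change per day | 0.91 to 0.95 | 0.19 to 0.27 |
| Mean signed change per day, better and worse balanced | about 0 | about 0 |

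A wider set of assumptions (daily rate 0.2 to 0.5, share of large changes 0.2 to 0.5) gives 0.90 to 0.98 and 0.00 to 0.34 for absolute values. If 70% of changes are for the worse, the signed mean correlates about −0.5 with frequency.

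**5. What this would do in the adherence model.** Further assumptions: n = 50, two-sided 0.05, likelihood-ratio test, intensity taken from mean absolute change per day.

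| Truth | Intensity alone, continuous | Intensity alone, tertiles | Intensity with frequency also in the model |
|---|---|---|---|
| Only frequency acts, OR 2 per SD | 57% reject | 40 to 44% reject | 6% reject |
| Only size acts, OR 2.5 per SD | 11% reject | not used | 47% reject |

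With no frequency effect and no size effect, intensity alone rejects in about 6 to 7%, close to nominal for this small sample. Mean size on fluctuation days as a continuous term rejects in 5 to 6% when only frequency acts, and has 39 to 45% power when only size acts. Cut into tertiles, it rejects in 9 to 16% although size has no effect, because it takes few distinct values and the classes are sparse.

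**The case against.** The strongest reply is that the article does not commit to the reading that causes the trouble.

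- It does not say that all 14 days enter, or that absolute values are used. The coding sentence ties the scores to reported health events, which could mean event days only. The per-day wording could even describe a display by diary day. This stands as ambiguity. However, a code for unchanged days has little purpose if only fluctuation days count, and pooling better with worse under a ± sign points to absolute values. The signed alternative does not measure size either.
- The per-day mean appears among the descriptive statistics, and nothing ties the low, moderate and high classes to it. Their cut-offs may be in a fuller plan. This stands, and it makes the regression consequence conditional.
- Frequency is counted separately, and the article plans to relate occurrence, frequency and intensity each to the consideration of fluctuations. This also stands. A reader might infer that the study cannot separate two of its own outcomes. It can: size on fluctuation days is 14 × mean absolute change ÷ count, so the two planned summaries together recover it.
- The study is explorative and states no alpha. The rejection rates need an assumed frequency effect. This stands, although such an effect is part of the stated hypothesis.

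The identity, the misranking and the cancellation need neither a simulation nor the link to the regression.

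**Conclusion.** The point holds as a badly fixed measure. On either the absolute all-days reading or the signed reading, the stated summary does not represent the size of fluctuations. In absolute values it is mostly frequency (correlation about 0.9 under the assumed rates). In signed values it cancels when better and worse days balance.

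The effect on the adherence analysis is a risk, not an established error. A reader might infer that the regression on intensity will reject because of frequency. That would require the three classes to be derived from this mean in absolute values, a real frequency effect, and no frequency term. The article supports only the last of these, and only for the one model it details. The 57% and the 40 to 44% show the size of the risk under those conditions; they are not a prediction for this study.

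**What to change.** In Quantitative data preparation and analyses:

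1. State that absolute values of the daily rating are used. Report intensity as the mean absolute change on days with a fluctuation, or as the share of those days rated ±2.
2. If mean absolute change per day is kept, label it overall fluctuation burden.
3. In the adherence model, enter the number of fluctuation days beside the intensity term, and say how the intensity term is derived. A continuous term is preferable, since three classes are sparse with 50 dyads.

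No new data are needed. The model gains one term. Intensity on fluctuation days is undefined for dyads with no fluctuation. Their number is unknown: the Discussion expects most patients to fluctuate, but the Sample size section asks only for at least 20 patients with fluctuations, which would leave up to 50 − 20 = 30 without. Using mean absolute change per day together with the number of fluctuation days in the model keeps those dyads in and still separates the two attributes, as the 6% and 47% above show.
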